## Abstract

**Introduction:**

The clinical symptoms of Lumbar Disc Herniation (LDH) can be effectively ameliorated through Lever Positioning Manipulation (LPM), which is closely linked to the brain's pain-regulating mechanisms. Magnetic Resonance Imaging (MRI) offers an objective and visual means to study how the brain orchestrates the characteristics of analgesic effects. From the perspective of multimodal MRI, we applied functional MRI (fMRI) and Magnetic Resonance Spectrum (MRS) techniques to comprehensively evaluate the characteristics of the effects of LPM on the brain region of LDH from the aspects of brain structure, brain function and brain metabolism. This multimodal MRI technique provides a biological basis for the clinical application of LPM in LDH.

**Methods and analysis:**

A total of 60 LDH patients and 30 healthy controls, matched by gender, age, and years of education, will be enrolled in this study. The LDH patients will be divided into two groups (Group 1, *n* = 30; Group 2, *n* = 30) using a random number table method. Group 1 will receive LPM treatment once every two days, for a total of 12 times over 4 weeks. Group 2 will receive sham LPM treatment during the same period as Group 1. All 30 healthy controls will be divided into Group 3. Multimodal MRI will be performed on Group 1 and Group 2 at three time points (TPs): before LPM (TP1), after one LPM session (TP2), and after a full course of LPM treatment. The healthy controls (Group 3) will not undergo LPM and will be subject to only a single multimodal MRI scan. Participants in both Group 1 and Group 2 will be required to complete clinical questionnaires. These assessments will focus on pain intensity and functional disorders, using the Visual Analog Scale (VAS) and the Japanese Orthopaedic Association (JOA) scoring systems, respectively.

**Discussion:**

The purpose of this study is to investigate the multimodal brain response characteristics of LDH patients after treatment with LPM, with the goal of providing a biological basis for clinical applications.

**Trial registration number:**

https://clinicaltrials.gov/ct2/show/NCT05613179, identifier: NCT05613179.

## Introduction

Lumbar disc herniation (LDH) primarily manifests as lower back and leg pain [1, 2]. This condition is distinguished by its high incidence, significant disability rate, and the absence of specific pharmaceutical remedies, thereby imposing a substantial socioeconomic burden on society [3–5]. In a comprehensive global disease survey encompassing 291 conditions, LDH holds the highest rank in terms of disability, with a prevalence rate of 9.4% [6]. Furthermore, it exhibits a noticeable trend towards affecting a younger demographic, with an escalating risk of disability as age advances [7]. Surgical treatment is a commonly employed clinical approach, yet concerns arise due to its recurrence rate and potential complications. Surveys indicate that 2.7% of individuals experience postoperative complications [8], with a 5-year reoperation rate reaching 11% [9, 10]. In contrast, non-surgical treatments are garnering increasing support from both medical practitioners and patients.

Lever positioning manipulation (LPM) is a supplementary therapeutic method for Lumbar Disc Herniation (LDH) and is extensively utilized in China [11, 12]. This technique is generally performed by skilled medical professionals who exert a controlled force on the patient's lower back muscles and spine to mitigate pain. However, the fundamental mechanisms underlying the pain relief provided by LPM, as well as the neurophysiological regulation of LPM by the brain, are not yet fully understood. Recent research postulates that pain relief results from the profound integration of incoming signals within the brain [13–16]. Consequently, the core mechanisms by which LPM alleviates pain in LDH necessitate a profound exploration into how the brain orchestrates pain sensitivity.

Magnetic resonance imaging (MRI) is a radiation-free technology characterized by exceptional spatial and temporal resolution, enabling non-invasive examination of the human brain [17–19]. This approach allows for the direct study of the human body, circumventing the limitations associated with reliance on animal models. In recent years, the investigation of the mechanisms by which the brain exerts analgesic effects through MRI has emerged as the cutting-edge and focal point of this discipline.

Functional magnetic resonance imaging (fMRI) stands as the most extensively employed technique within the realm of MRI, notable for its heightened sensitivity in scrutinizing the cerebral functional attributes. A multitude of studies have consistently emphasized that the brain's functional alterations take precedence over structural changes [19, 20]. At present, prevalent data analysis methods for resting-state fMRI encompass the examination of metrics such as mean amplitude of low-frequency fluctuation (mALFF) [21], regional homogeneity (ReHo) [22], and functional connectivity (FC) [23]. Moreover, magnetic resonance spectroscopy (MRS) represents an additional technical modality within the MRI domain, being the sole non-invasive means for quantitatively detecting alterations in cerebral substances [24, 25]. MRS can discern a plethora of compounds within the brain, including N-acetylaspartate (NAA), choline (Cho), creatine (Cr), glutamate (Glu), glutamine (Gln), gamma-aminobutyric acid (GABA), and glucose, among others. Consequently, MRS serves as a supplementary avenue of research to fMRI, facilitating a more profound exploration of metabolic changes within the implicated brain regions.

This study employs multimodal MRI techniques, specifically ALFF and ReHo, to analyze crucial brain regions associated with analgesic effects. Subsequently, statistically significant differences in brain regions are extracted as regions of interest (ROI) for the analysis of brain network FC. This analysis is aimed at monitoring neurochemical changes related to MRS within the ROI brain regions, with the overarching goal of investigating the neuroimaging mechanisms behind the analgesic efficacy of LPM in the context of LDH.

## Materials and methods

### Study design

This non-randomized clinical trial is set to enroll 60 patients diagnosed with Lumbar Disc Herniation (LDH) and 30 healthy controls (HCs). Fig. 1 illustrates the schematic outline of the study protocol. The research protocol has received approval from the Institutional Review Board (No. ZSLL-KY-2022–049-01) at the Third Affiliated Hospital of Zhejiang Chinese Medical University, P. R. China. Additionally, this protocol is registered on ClinicalTrials.gov (registration No. NCT 05613179). Written informed consent for participation will be obtained from all participants involved in this study.

**Fig. 1 Fig1:**
[figure not shown]
Standard protocol items: recommendations for interventional trials (SPIRIT) schedule of the trial

### Participants

Sixty patients with LDH and thirty with HCs will be recruited for this study. All 60 LDH patients were randomly divided into 2 groups with 30 patients in each group. The Group1 will be treated with LPM and Group2 will be treated with sham LPM.

Inclusion criteria for the LDH patients are as follows: participants must meet the diagnostic criteria for lumbar disc herniation, including protrusion types such as central, paracentral, far lateral, foraminal, and subarticular, with imaging findings that align with neurological localization. The age range for participants is 18 to 65 years, encompassing any gender, and they must be right-handed. Participants should be in the non-acute phase of the condition, experiencing mild to moderate pain and functional impairment, with the duration of symptoms exceeding 2 weeks. They should have a Visual Analog Scale (VAS) score greater than 4 and Japanese Orthopaedic Association (JOA) scores less than 15 [26]. Eligible participants must not have taken analgesics, neurotropic nutrition drugs, or sedatives in the past month and should not have undergone systemic treatment. Additionally, they should not have received spinal manipulation or other physical therapies in the past month. Finally, participants must voluntarily agree to participate in this study and have signed an informed consent form.

Exclusion criteria for the study are as follows: (1) Patients with concurrent internal medicine or gynecological conditions known to cause lower back pain, such as nephritis, urinary stones, gynecological inflammations, and uterine abnormalities. (2) Individuals with severe primary diseases impacting the cardiovascular, cerebrovascular, liver, or kidney systems. (3) Those with neurogenic functional disorders, psychiatric conditions, a history of significant head trauma, or a history of unconsciousness. (4) Individuals diagnosed with primary sciatica or dry sciatica. (5) Those with lumbar spondylolisthesis. (6) Patients suffering from lumbar tumors or tuberculosis. (7) Individuals with severe osteoporosis or localized skin lesions in the lumbar area. (8) Patients experiencing painful conditions beyond the lumbar region. (9) Those with diseases characterized by structural changes in the brain. (10) Individuals with impaired consciousness, severe visual or hearing impairments, speech disorders, or others who are unable to complete health assessments. (11) Individuals with dental implants, metal stents, or other elements that may compromise MRI imaging. (12) Those with a fear of MRI or other reasons that prevent undergoing MRI scans. (13) Patients diagnosed with lumbar disc herniation but who are asymptomatic.

We recruited age- and gender-matched healthy controls with no history of Lumbar Disc Herniation (LDH) (Group 3) through poster advertisements. The eligibility criteria for these participants were as follows: they must be right-handed, aged between 18 and 65 years, and of any gender. These individuals should have no history of lower back pain and must not have received any medication or undergone relevant physical therapy in the past month. Additionally, they should have a clear understanding of the research process and express willingness to participate by signing the informed consent form.

### Participant recruitment

All patients with LDH and HCs will be recruited from both outpatient and inpatient services of the Third Affiliated Hospital of Zhejiang Chinese Medical University, P. R. China, as well as from the community through advertising campaigns. The recruitment period is set from September 2021 to September 2025.

### Randomization, allocation concealment, and blinding

After baseline assessments, eligible participants with LDH will be randomly allocated to either the LPM group or the sham-LPM group through a randomization process. A random number grouping table will be generated based on the predetermined number of cases and a specified random proportion. These randomization tables will be created using SAS 9.0 software and will be managed by independent research assistants who are not involved in the participant recruitment, assessment, or intervention processes.

Independent research assistants will inform eligible participants of their group assignment results via phone communication. Due to the nature of the interventions, it is not possible to implement blinding for researchers, participants, and practitioners throughout the course of the experiment. However, laboratory technicians and researchers responsible for conducting statistical analyses will be kept blinded to group assignments to ensure the objectivity and integrity of the data analysis.

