### Procedure

Multimodal fMRI and MRS scans were conducted for patients with LDH in Group 1 and Group 2 at three distinct time points (TPs): before LPM (time point 1, TP1), within one hour after the first intervention (Group 1 receiving LPM and Group 2 receiving sham LPM) (time point 2, TP2), and within one hour after the last intervention (Group 1 with LPM and Group 2 with sham LPM) (time point 3, TP3).

Patients in Group 1 and Group 2 were additionally required to fill out clinical questionnaires before undergoing the multimodal fMRI and MRS scans at two time points. They were instructed to rate the severity of their LDH symptoms using the VAS, where 0 represents 'no pain' and 10 indicates the 'strongest imaginable pain', and to complete the JOA assessment forms. The differences in VAS and JOA scores between these two time points were calculated to assess changes in pain and functional status.

For the healthy controls in Group 3, only a single session of multimodal fMRI and MRS scan was performed, and they did not participate in completing any clinical questionnaires.

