**Fig. 2 Fig2:**
[figure not shown]
Lever positioning manipulation (LPM) operation diagram: **A** Massaging and manipulation for lumbar muscular relaxation. **B** LPM

Sham-LPM Treatment: All preparatory steps, patient positioning, and the duration before the commencement of Sham-LPM were identical to those of the LPM treatment, thus effectively minimizing operational bias. The key difference in sham-LPM is that when the patient's position reaches the critical point, the operator does not perform a swift twisting motion. Instead, a protective belt is used to maintain the patient’s position unchanged (Fig. 2).

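### Participants are told by phone whether they are in the LPM or the sham arm, so the sham no longer protects the comparison against expectation and reporting bias

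*Protocol article*

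**What the plan says.** The section on randomization, allocation concealment and blinding names the two arms as LPM and sham-LPM and then states: "Independent research assistants will inform eligible participants of their group assignment results via phone communication". Giving the nature of the interventions as the reason, it adds that "it is not possible to implement blinding for researchers, participants, and practitioners throughout the course of the experiment". The only people kept unaware are named in the next sentence: "laboratory technicians and researchers responsible for conducting statistical analyses will be kept blinded to group assignments".

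The Participants section sets up the control: "The Group1 will be treated with LPM and Group2 will be treated with sham LPM". The sham description, in the section on Lever Positioning Manipulation, says "All preparatory steps, patient positioning, and the duration before the commencement of Sham-LPM were identical to those of the LPM treatment", and gives the purpose as "thus effectively minimizing operational bias". The difference comes at the critical point, where the operator omits the swift movement and a protective belt holds the patient in position.

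The Procedure section makes the patient the source of the clinical data: "They were instructed to rate the severity of their LDH symptoms using the VAS". Patients also complete the JOA forms. The TP2 scan is taken "within one hour after the first intervention (Group 1 receiving LPM and Group 2 receiving sham LPM"), and TP3 likewise follows the last session.

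**The concern.** A sham matched this closely can control for what the patient expects, but only if the patient is not told which procedure it is. Here the plan builds the matched procedure and then discloses the arm. From that call onward the two groups differ in two respects: whether the thrust is delivered, and whether the patient believes the treatment is real.

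The clinical outcomes are completed by the patient, so belief can alter both the pain experienced and the score reported. The imaging outcomes are exposed too. The stated aim is to explain how LPM produces analgesia through the brain, and expecting relief is itself a brain process. A difference between arms at TP2 or TP3 could reflect the manipulation, the belief, or both, and the design would offer no means of separating them. Randomization does not help, because the difference in belief arises after allocation. Blinded analysis does not help either, because the data are already affected when the analyst receives them.

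**Working it through.** **Step 1: set the statements side by side.**

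| Element | What the protocol article states | Consequence |
|---|---|---|
| Sham procedure | Preparation, positioning and time before the manoeuvre match LPM; the final movement is omitted | Handling and contact time are controlled |
| Disclosure | Arm given to each participant by phone | Expectation differs between arms |
| Reason given | Nature of the interventions | Covers the practitioner, who must know whether to deliver the thrust; does not require telling the patient |
| Who is blinded | Laboratory technicians and statistical analysts | Does not reach the patient, who completes VAS and JOA |
| Scan timing | TP2 and TP3 within one hour after an intervention | The patient already knows the arm at both scans |

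The call cannot easily be read as passing on a neutral code. The section names the arms as LPM and sham-LPM, and its next statement says that participants are not blinded.

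**Step 2: illustrate the possible size.** The document gives no significance level, effect size or SD for the LPM-versus-sham comparison of VAS, so there is no figure of its own to reproduce.

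Inputs:
- n = 30 per arm (Participants section)
- two-sided α = 0.05 (assumed)
- no true effect of LPM (assumed, to isolate the disclosure effect)
- a shift of d SD between arms caused by disclosure alone (assumed, range 0 to 0.5)

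Formula, normal approximation for two means: the noncentrality is δ = d × √(n/2) = d × √15 = 3.873 d. The probability of a significant result is Φ(δ − 1.96) + Φ(−δ − 1.96).

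| Assumed shift d (SD) | δ | Chance of a significant difference |
|---|---|---|
| 0 | 0 | 5.0% |
| 0.2 | 0.77 | 12.1% |
| 0.3 | 1.16 | 21.3% |
| 0.5 | 1.94 | 49.1% |

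**Step 3: limit of the illustration.** It describes one test of one continuous outcome. The imaging contrasts use a voxel threshold of P < 0.005, clusters of at least 50 voxels and an FDR correction (Image viewing section), so these percentages do not carry over to ALFF, ReHo or FC.

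**The case against.** The best defence is that blinding might fail even without the call. LPM involves a rapid pull during which the practitioner feels for a click or loosening, whereas the sham holds the patient still with a belt. The matching is stated only for the phase before the manoeuvre, and the abstract gives 12 sessions, so some patients could work out their arm. This stands: withholding the label cannot be promised to give complete blinding. It is a reason to measure what patients believe, but not a reason to disclose the arm to all of them. Eligible patients have had no spinal manipulation in the past month, so they have no recent experience to compare with.

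Three further points stand in part:
- **Purpose of the sham.** The article states its purpose only as limiting operational bias. A reader might infer that disclosure makes the sham worthless. The text does not support that, because handling, positioning and preparatory time remain matched.
- **Staff.** Laboratory technicians are blinded, and this may or may not include the MRI operators. No separate collector of VAS or JOA is described. It would go too far to say that the scan staff are unblinded; the wording needs clarifying.
- **Baseline.** Randomization follows the baseline assessments, and the scan is scheduled for the day of enrolment. A reader might infer that TP1 is also affected. The order of the TP1 scan and the call is not explicit, so the text supports a request for clarification and no more.

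**Conclusion.** The concern holds in this form: the plan discloses the arm to participants without a reason that requires it, and so gives up the sham's protection against expectation and reporting bias. LPM-versus-sham differences in VAS, JOA, ALFF, ReHo, FC and MRS after TP1 are at risk of confounding with expectation. This affects the trial's central comparison.

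The size is unknown. The range of about 12% to 49% false positives rests entirely on assumed shifts of 0.2 to 0.5 SD, a single two-sided 5% test, 30 per arm and no true effect. It is not an estimate for this trial. A reader might infer that the results are biased by a known amount, or that the imaging contrasts carry the same error rates. The document supports neither: it gives nothing from which to size the shift, and the imaging thresholds are of a different kind.

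**What to change.** 1. Delete the phone disclosure. The research assistants give participants appointment times only and release the arm to the practitioner alone, after the TP1 scan.
2. Restate the blinding section so that participants, any staff who handle VAS or JOA, MRI operators and analysts stay unaware of the arm until TP3 is complete. State whether laboratory technicians include the MRI operators.
3. Ask participants to guess their arm after TP2 and after TP3, and report the guesses by arm, since blinding may be incomplete.
4. Recruitment was planned from September 2021 to September 2025, so many or all participants may already have been told. For them, describe the trial as open-label to participants and limit the mechanistic claims accordingly. If the rule changes partway through, report results before and after the change as a descriptive sensitivity analysis only: the split divides 30 per arm into smaller, non-concurrent groups.

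The cost is an amendment, revised consent wording and one extra question. Participants already told cannot be re-blinded.

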### Procedure

Multimodal fMRI and MRS scans were conducted for patients with LDH in Group 1 and Group 2 at three distinct time points (TPs): before LPM (time point 1, TP1), within one hour after the first intervention (Group 1 receiving LPM and Group 2 receiving sham LPM) (time point 2, TP2), and within one hour after the last intervention (Group 1 with LPM and Group 2 with sham LPM) (time point 3, TP3).

Patients in Group 1 and Group 2 were additionally required to fill out clinical questionnaires before undergoing the multimodal fMRI and MRS scans at two time points. They were instructed to rate the severity of their LDH symptoms using the VAS, where 0 represents 'no pain' and 10 indicates the 'strongest imaginable pain', and to complete the JOA assessment forms. The differences in VAS and JOA scores between these two time points were calculated to assess changes in pain and functional status.

For the healthy controls in Group 3, only a single session of multimodal fMRI and MRS scan was performed, and they did not participate in completing any clinical questionnaires.

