#### Multimodal fMRI and MRS Scan

Participants in this study were recruited and evaluated at the Massage Department of the Third Affiliated Hospital of Zhejiang Chinese Medical University. Those who met the inclusion criteria underwent data collection using a Siemens Skyra 3.0 T superconducting MRI scanner at Zhejiang Hospital (MAGNETOM Skyra 3.0 T, Siemens, Germany). To minimize confounding factors, clinical interventions for patients with LDH were consistently performed at Zhejiang Hospital, with MRI data collection taking place within 1 h of completing the intervention.

For the LDH group, multimodal fMRI and MRS scans were conducted both before and after immediate treatment. Conversely, the healthy control group underwent a single session of multimodal fMRI and MRS scanning at the time of their enrollment. It is common for patients to experience more pronounced pain sensations on the day of their medical consultation. Hence, to ensure the timely acquisition and reliability of brain function data in response to pain stimuli, MRI scans were conducted on all study participants on the same day they were enrolled and had completed their baseline data assessment.

For structural imaging, a Gradient echo sequence 3D-T1 will be utilized with the following parameters: 249 slices, repetition time (TR) of 2530 ms, echo time (TE) of 2.89 ms, slice thickness of 1.2 mm, layer spacing of 1.0 mm, voxel size of 1 mm × 1 mm × 1 mm, flip angle of 9°, field of view (FOV) of 256 mm × 256 mm, and a data matrix of 64 × 64. The duration of the 3D-T1 sequence will be approximately 5 min and 53 s.

FMRI scans will be acquired using an echo-planar imaging sequence with these settings: 43 slices, TR of 2680 ms, TE of 30 ms, slice thickness of 3.0 mm, no gap, voxel size of 3 mm × 3 mm × 3 mm, flip angle of 9°, FOV of 192 mm × 192 mm, and a data matrix of 64 × 64. The functional sequence will take about 10 min and 53 s.

MRS scans will be conducted using a PRESS (Point-Resolved Spectroscopy) sequence with these parameters: TR of 1700 ms, TE of 35 ms, slice thickness of 2.0 mm, no gap, voxel size of 10 mm × 10 mm × 10 mm, FOV of 240 mm × 240 mm, and a data matrix of 128 × 128. The PRESS sequence will take approximately 9 min and 13 s.

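### LDH patients are scanned at three time points but rate pain and function at only two, so one post-treatment scan probably has no concurrent pain score

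*Protocol article*

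**What the plan says.** The Procedure section gives Groups 1 and 2 three multimodal scans. TP1 is before LPM, TP2 is "within one hour after the first intervention", and TP3 is "within one hour after the last intervention". The Abstract gives the same three scans.

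The next paragraph of Procedure turns to VAS and JOA. Patients are "additionally required to fill out clinical questionnaires before undergoing the multimodal fMRI and MRS scans at two time points". It then defines the clinical change measure: "The differences in VAS and JOA scores between these two time points were calculated to assess changes in pain and functional status". The labels TP1, TP2 and TP3 have just been introduced but are not used here. The Abstract requires the questionnaires without giving their timing.

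The section on the multimodal scan describes the schedule a second time, differently: "For the LDH group, multimodal fMRI and MRS scans were conducted both before and after immediate treatment". It does not mention a scan after the full course.

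Two statements bear on whether baseline is one of the two questionnaire points. The eligibility criteria under Participants include pain and function scores: "They should have a Visual Analog Scale (VAS) score greater than 4", with a JOA limit alongside. The scan section places the first scan "on the same day they were enrolled and had completed their baseline data assessment".

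**The concern.** The last paragraph of the Introduction sets the aim: to explain, through imaging, how LPM relieves pain in LDH. Both post-treatment scans serve that aim. TP2 captures the response to one session, and the Discussion reports that the preliminary experiments saw widespread, immediate brain activation. TP3 captures the response to the whole course of 12 sessions over 4 weeks.

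To read a brain change as part of pain relief, one needs to know whether pain fell in these patients at that time, and whether it fell more with LPM than with sham. The current text provides two questionnaire occasions and one change score for three scans. That is a stated schedule, not a detail left to a fuller document. It also leaves open whether the only clinical change score covers one session or four weeks.

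**Working it through.** No power, alpha or sample-size figure is involved. The check is a count of assessments followed by a comparison of the possible pairings.

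**Count (Procedure).** Scan time points per LDH patient: 3. VAS/JOA time points: 2. Scans without a questionnaire: 3 − 2 = 1.

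**Which scan is unscored.** Two points can be chosen from three in three ways:

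| Questionnaires at | Scan without VAS/JOA | Consequence |
|---|---|---|
| TP1 and TP2 | TP3 | The change score covers one session; pain and function after the full course are not measured |
| TP1 and TP3 | TP2 | The full-course change is measured; the immediate brain response has no same-time pain score |
| TP2 and TP3 | TP1 | Both post-treatment scans are scored, but the single change score leaves out baseline |

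**Is the third pairing plausible?** It fits the text poorly. A TP3 − TP2 difference runs from after the first session to after the last, so it is not the change from before treatment. VAS and JOA are needed at entry to establish eligibility, and the baseline assessment is completed on the day of the first scan. These points support TP1 as one of the two, but that is an inference, since Procedure does not say so.

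**Planned scale.** With 60 patients and two post-baseline scans each, 60 × 2 = 120 post-baseline scans are planned. Under either of the first two pairings, 60 × 1 = 60 of them have no concurrent VAS. This assumes no dropout and no unusable scans, and it only restates one scan in two per patient. It does not measure bias or lost power.

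**What the imaging analyses need.** The sections on calculation and image viewing select regions by differences in ALFF and ReHo, carry those regions into FC, and measure metabolites by MRS. None of these steps uses VAS or JOA, so the contrasts can be computed at every scanned time point. What is missing at the unscored scan is the clinical reading of the result.

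**The case against.** The strongest reply is that the figure most likely to settle the timing, Fig. 1, was not visible in the text reviewed. A SPIRIT schedule may well name the two questionnaire points. That stands, and it limits confidence. Naming them would remove the ambiguity, but by itself it would not turn two assessments into three.

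A second reply is that no correlation between brain measures and pain is pre-stated, and that the imaging contrasts, including LPM versus sham at TP2 and TP3, need no VAS. This also stands. A reader might infer that a planned analysis becomes impossible, or that a brain change at the unscored scan can never be called analgesic. The article does not support that. The loss is to interpretation against the stated aim. If VAS is taken at TP1 and TP3, the full-course response is anchored and TP2 can still be reported as an early brain response compared with sham.

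Third, the two consequences exclude each other. A reader might infer that the full-course outcome is never measured, but that holds only if the pair is TP1 and TP2. The other pairing is considerably milder, and the article does not show which applies.

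Fourth, the scan section's wording about immediate treatment might be taken to put the full-course scan in doubt. Procedure and the Abstract both state three scans clearly, so this is better treated as loose wording to be aligned.

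**Conclusion.** The point holds as a moderate-confidence design weakness. Three scans and two questionnaire occasions are stated, and no visible text adds a third VAS. If baseline is one of the two, one of the two post-treatment scans per patient has no concurrent pain score. At TP3 this would mean that the clinical change over the full course is not measured. At TP2 it would mean that the immediate brain response cannot be related to pain relief, or to an LPM-versus-sham pain difference, at the same moment.

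The planned ALFF, ReHo, FC and MRS contrasts remain valid to compute. Their interpretation as analgesic at the unscored time point, which is what the trial sets out to explain, has no within-trial support. Describing this as half of the post-treatment scans being lost would overstate it, because the scans remain usable and the fraction only repeats the count.

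The conclusion rests on two assumptions: that TP1 is one of the two questionnaire points, and that Fig. 1 does not add a third VAS.

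**What to change.** In Procedure:
- Collect VAS before the scan at TP1, TP2 and TP3. At TP2 and TP3, say that the rating falls after the session and before the scan, because the present wording fixes it only relative to the scan.
- State JOA at TP1 and TP3.
- Name the time points behind each change score: TP2 − TP1 and TP3 − TP1 for VAS, TP3 − TP1 for JOA.

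In the section on the multimodal scan, replace the wording about before and after immediate treatment with the three-scan schedule. Check that Fig. 1 agrees with both.

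The cost is one additional 0–10 rating per patient at a visit that already takes place, plus the amendment text. The drawback is timing. Recruitment is set to run from September 2021 to September 2025, and the article does not say how many patients have still to reach the unscored visit. Those already past it cannot supply the rating, so VAS at that point will be partial and should be reported as such, with the number of patients contributing in each group.
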